### Standards of excluded and dropout cases

#### Standards of dropout cases

All participants have the right to terminate the clinical trial at any time. Subjects who do not complete the clinical trial will be considered dropout cases. The common causes of dropouts are as follows: adverse events, lack of efficacy, violation of the trial plan, lost to follow-up (including the subjects or their guardians who decided to terminate the treatment), and other reasons.

#### Dropout cases

For dropout cases, the researchers will specify the reason for dropping out in the CRF. At the same time, the researchers will contact the guardians and complete the assessment items; the causes for dropping out will be made clear and specified in the CRF. The observational data on all dropout cases will be preserved for statistical analysis at the end of the trial.

#### Excluded cases

If the cases included conform to one of the following, they will be excluded: mistakenly included; and lack of treatment. The reason for a case being excluded will be specified. The CRF will be preserved for future reference. Statistical analysis of the efficacy data will not be carried out, however, the subjects who receive at least one treatment session will be included in the analysis of adverse reactions.

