### Intervention

Subjects in the acupuncture group will wear SVLs. Acupuncture will be performed at five acupuncture points (bilateral Cuanzhu (BL2), Tongziliao (GB1), Sibai (ST2), Muchuang (GB16), and Hegu (LI4), see Figures 
2 and
3). Alcohol (75%) will be used to routinely disinfect the local skin at the acupuncture points and 0.25 mm × 0.4 mm disposable sterile acupuncture needles (Suzhou Acupuncture & Moxibustion Appliance Co., Ltd., Suzhou, China) will be used at acupuncture points Sibai and Hegu to a depth of 0.5 to 1.0 cm. After achieving *de-qi* (Subjects have a feeling of soreness, fullness, aching, heaviness at and around the acupoints), the needle will be held in position for 20 minutes. Cuanzhu will be acupunctured to a depth of 0.3 to 0.5 cm. Tongziliao and Muchuang will be acupunctured to a depth of 0.1 to 0.3 cm. After achieving *de-qi*, the needle will be held in position for 20 minutes. Acupuncture will be carried out once a day between 10:00 and 19:00 (Beijing time). One cycle of treatment will last for nine days, followed by one day of no treatment. Six cycles of treatment will be undertaken continuously for a total of 60 days. The acupuncturist in this study, a physician with 18 years of experience in clinical acupuncture, will not participate in objective examinations, such as visual acuity. Subjects in the control group will wear SVLs without any other treatment affecting visual acuity. Observations will be carried out for two consecutive months.

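### The efficacy exclusion for lack of treatment is undefined, is not confined to the per-protocol set, and can in practice remove randomised children from the acupuncture arm only

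*Protocol article*

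**What the plan says.** Four parts of the protocol article bear on this.

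- **Excluded cases.** Of cases meeting either of two conditions it says "they will be excluded: mistakenly included; and lack of treatment". The consequence, where the inclusion meant is in the safety analysis only, is: "Statistical analysis of the efficacy data will not be carried out, however, the subjects who receive at least one treatment session will be included". No number of sessions is given, and no analysis set is named.
- **Standards of dropout cases** and **Dropout cases.** "Subjects who do not complete the clinical trial will be considered dropout cases". The listed causes include breaking the trial plan and "lost to follow-up (including the subjects or their guardians who decided to terminate the treatment"). For these children, "The observational data on all dropout cases will be preserved for statistical analysis at the end of the trial", and the researchers are to contact the guardians and complete the assessments.
- **Statistical analysis.** Primary and secondary outcomes are to be analysed by intention to treat, using both the FAS and the PPS.
- **Intervention** and **Recruitment strategies.** The acupuncture arm has six cycles of nine daily sessions. In the other arm, "Subjects in the control group will wear SVLs without any other treatment affecting visual acuity". Compliance is judged by whether the treatment due was received, and the stress on regular attendance is directed at the experimental group.

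**The concern.** Intention-to-treat protects the comparison because every randomised child is counted in the arm drawn, whatever happens afterwards. A rule that drops children from efficacy because they were not treated uses a post-randomisation event to decide who is counted. Here that event can be observed in practice only in the acupuncture arm. Both arms wear single-vision lenses, and the article describes no check of lens wear, so a control child from a family that would have skipped sessions cannot be recognised and stays in.

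If the rule governs the main efficacy analysis, the trial compares acupuncture children who were treated with all controls. Any link between attendance and myopia progression (family habits, outdoor time, severity) then enters the estimate as if it were a treatment effect. The article also keeps the data of children who stop treatment, so the same child may be kept or dropped depending on which heading is applied, and no order of precedence is given.

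**Working it through.** **1. Which rule applies to which child**

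| Child in the acupuncture arm | Dropout sections | Excluded cases | Intention-to-treat statement |
|---|---|---|---|
| Never starts and leaves the trial | Non-completer: data kept | Lacks treatment on any reading: no efficacy analysis | Counted |
| Never starts but attends visits | Not clearly a dropout | Lacks treatment on any reading: no efficacy analysis | Counted |
| Starts, then stops treatment | Named as a dropout: data kept | Excluded only if partial treatment counts as lack of treatment | Counted |
| Misses some sessions, attends visits | Not clearly a dropout, though breaking the plan is a listed cause | Excluded only if partial treatment counts | Counted |

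In the first two rows the exclusion contradicts intention-to-treat on any reading. In the first it also contradicts the dropout rule. In the last two the conflict depends on the undefined term.

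**2. Which arm is affected**

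Sessions due: acupuncture 6 × 9 = 54; control 0. The other ground, mistaken inclusion, can arise in either arm. The lack-of-treatment ground has a described counterpart only in the acupuncture arm.

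**3. Illustration of size**

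The protocol gives no figure to reproduce on this point. From the document: 50 per arm, SD 0.25 D, one-sided 5% level with critical value 1.645. Assumed, with no source in the document: no true effect; a test against a difference of zero; a fraction p of each arm would not attend; those children do worse by d; exclusions occur in the acupuncture arm only.

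- The mean of all randomised children is the mean of the attenders minus p × d. Dropping non-attenders from one arm therefore shifts the difference by p × d.
- SE = 0.25 × √(1/(50(1 − p)) + 1/50)
- Error = 1 − Φ(1.645 − p × d / SE)

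| p | d (D) | Shift (D) | SE | Shift/SE | One-sided error |
|---|---|---|---|---|---|
| 2% | 0.125 | 0.0025 | 0.0503 | 0.05 | 5.5% |
| 4% | 0.125 | 0.005 | 0.0505 | 0.10 | 6.1% |
| 10% | 0.125 | 0.0125 | 0.0514 | 0.24 | 8.1% |
| 10% | 0.25 | 0.025 | 0.0514 | 0.49 | 12.3% |
| 20% | 0.125 | 0.025 | 0.0530 | 0.47 | 12.0% |
| 20% | 0.25 | 0.05 | 0.0530 | 0.94 | 24.1% |

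Simulation with a pooled t-test gives slightly lower values, about 22% in the last row.

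**4. Two sensitivities**

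- Direction: if the excluded children do better by the same amount, the last row becomes 1 − Φ(1.645 + 0.943) = 0.5%, and the bias runs against acupuncture.
- Null hypothesis: if the 0.2 boundary in the sample-size section is what is tested, the last row becomes 1 − Φ(1.645 + (0.2 − 0.05)/0.0530), about 0.000004. The table therefore applies only to an ordinary test against zero.

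**The case against.** The best defence is that lack of treatment means never treated. The dropout wording about ending treatment presupposes that it began, so never-starters would be excluded and those who stop would be dropouts. The clause keeping children with at least one session in the safety analysis could then refer only to those mistakenly included. Membership of the FAS and PPS is also commonly left to an analysis plan, which is not shown here.

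Much of this stands. A reader might infer that every child who misses sessions falls under both rules. The text does not establish that: the overlap is certain only for some children, such as one who never starts and leaves. A reader might also infer that the researchers who carry out the allocation decide the exclusions with the arm known. The article has them allocate subjects and record reasons for dropout, but the exclusion section does not say who decides, and the analysing statistician is described as blinded. Finally, a reader might take the upper error rates as the expected inflation in favour of acupuncture. The fraction, the difference and its sign all lack a source; the 20% in the sample-size section is a dropout rate, and 0.25 D is a full planning SD.

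The defence does not remove the point. Even on the narrow reading, randomised children who never start are barred from efficacy analysis, and in practice they can come only from the acupuncture arm. The complaint is not that set definitions are missing. The article states a bar on efficacy analysis, without confining it to the PPS, alongside a promise of intention-to-treat. An analysis plan would have to override one of the two.

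**Conclusion.** The point holds as an internal conflict with a foreseeable one-arm effect. The exclusion section bars efficacy analysis for an undefined lack of treatment. That contradicts the intention-to-treat/FAS commitment and partly overlaps with the rules that keep dropout data. Followed as written, it removes randomised children essentially from the acupuncture arm. That last step is an inference from the design: failure to wear lenses could in theory count for controls, but nothing described would detect it.

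The document does not allow the size or direction of bias to be derived. An error of about 5.5% to 24% against a nominal 5% is an illustration under the stated assumptions. The low end applies if very few children never start, and the high end needs a fifth excluded with outcomes one SD worse. Whatever the size, the comparison would no longer be the randomised one.

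**What to change.** Reword the section on excluded cases in three respects.

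1. Remove lack of treatment as a ground for exclusion from the FAS/intention-to-treat efficacy analysis and confine it to the PPS, with a definition.
2. State that children with few or no sessions are analysed in their randomised arm, with follow-up outcomes collected as the dropout section already provides.
3. Limit removal as mistakenly included to eligibility failures shown by data recorded before randomisation and judged without knowledge of the arm.

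The cost is one paragraph of wording. The estimated effect may be slightly smaller because children with little or no treatment stay in. The change restores the nominal 5% only as far as outcomes are actually obtained. Under Withdrawal conditions a withdrawn child's last result becomes final, so a non-starter seen only at baseline could be scored as unchanged. Collecting follow-up data on these children is therefore an essential part of the fix.

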### Recruitment strategies

The subjects will be informed of the details regarding the trial plan and those who voluntarily participate in the trial will receive free ophthalmologic examinations. Following optometric evaluation, these subjects will receive the highest discount (30% off) on glasses. Subjects in the experimental group will receive a 50% discount on acupuncture treatment. All subjects who receive a follow-up eye exam will not pay a fee and will be permitted to be fast-tracked. The subjects who will be included in the experimental group will receive treatment any time between 10:00 and 19:00 (Beijing time). If adverse events occur during treatment, the treatment will be immediately terminated, and help will be obtained from the emergency department. According to the specific condition which occurs after treatment, a consultation involving at least three experts will be carried out to decide whether or not to continue the clinical trial. Subject compliance will be determined based on whether or not the subject receives due treatment. The researchers will ensure that the subjects in the experimental group fully understand the importance of regular acupuncture and compliance. During the observation period, the use of drugs or other therapies to treat mild-to-moderate myopia will be prohibited.

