### Statistical analysis

All statistical analyses will be performed using SPSS 17.0 statistics software. For quantitative data, the distribution pattern and homogeneity of variance will be examined. If there is a symmetric distribution, the mean (M) ± standard deviation will be used for statistical description, otherwise the M interquartile range (IQR) will be used to describe the trend of concentration and amount of scatter. If this condition is met, the Student's t-test will be used to compare the differences between the quantitative indices between the groups, otherwise the Wilcoxon rank-sum test will be used. For categorical data (binary classification and multiple classification), the composition ratio will be used for statistical description. Based on the observation of a theoretical frequency distribution, the χ^2^ or Fisher's exact test will be used, depending on the specific situation. The ranked data will be analyzed using the Wilcoxon rank-sum test.

Primary and secondary outcomes will be analyzed by the superiority test in accordance with the principle of intention-to-treat, using Per Protocol Set (PPS) and Full Analysis Set (FAS) datasets. The indices of safety evaluation will be analyzed using the Save Set (SS) dataset. The significance level in this study will be set at α = 0.05, and the one-sided test will be used. The detailed statistical analytical methods for primary and secondary outcomes and baseline data are shown in Table 
2 (variables, measures, and methods of analysis).

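### The excluded-cases rule takes randomised children out of the efficacy analysis, contradicting the stated intention-to-treat principle, and in practice it falls mainly on the acupuncture arm

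*Protocol article*

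**What the plan says.** All references are to the protocol article.

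- **Excluded cases:** of children already included, it says "they will be excluded: mistakenly included; and lack of treatment". For these, "Statistical analysis of the efficacy data will not be carried out". Safety is handled separately: "the subjects who receive at least one treatment session will be included in the analysis of adverse reactions".
- **Statistical analysis:** primary and secondary outcomes are to be tested "in accordance with the principle of intention-to-treat, using Per Protocol Set (PPS) and Full Analysis Set (FAS) datasets". The article does not define either set.
- **Intervention:** "Subjects in the acupuncture group will wear SVLs", and they also have needling on nine days of each ten-day cycle for six cycles. "Subjects in the control group will wear SVLs without any other treatment affecting visual acuity".
- **Recruitment strategies:** "Subject compliance will be determined based on whether or not the subject receives due treatment".
- **Withdrawal conditions and Dropout cases:** two other categories are treated differently. For withdrawn children the last result stands as final. Data from dropouts are kept for the analysis.

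**The concern.** Intention-to-treat means that a randomised child is analysed in the assigned arm whatever treatment followed. A rule that removes children from efficacy analysis for not having been treated is the opposite, and nothing in its wording limits it to a per-protocol analysis.

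The rule also does not bear equally on the two arms. Lens wear is common to both, and sessions exist in one arm only. A family allocated to acupuncture faces 9 × 6 = 54 sessions in 60 days, at half price rather than free (Recruitment strategies), and no control family faces a comparable hurdle. Study design lists only assessors and the statistician as blinded, so whether a child takes up treatment can depend on the known allocation. Children who do not take it up may differ in motivation, reading habits or outdoor time. Removing them from one arm would leave a selected acupuncture group compared with an unselected control group. Neither the t-test nor the rank-sum test can repair that.

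**Working it through.** **1. The texts side by side**

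| Child | Section | Efficacy data |
|---|---|---|
| Withdrawn | Withdrawal conditions | Last result used |
| Dropout, including when the family ends treatment | Standards of dropout cases; Dropout cases | Kept |
| Mistakenly included | Excluded cases | Not analysed |
| Lack of treatment | Excluded cases | Not analysed |
| Any randomised child | Statistical analysis | Intention-to-treat |

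The third and fourth rows conflict with the fifth. Lack of treatment can be known only after allocation, so the fourth row is a post-randomisation exclusion. The second and fourth rows also have no clear boundary. A child who attends a few sessions and stops looks like a dropout, but no number of sessions is given that separates this from lack of treatment.

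**2. Which arm it falls on**

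Lenses are worn in both arms, so a rule about lenses could apply to either. The part that differs between arms is the sessions, which only the acupuncture arm has. Mistaken inclusion can occur in either arm.

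**3. Size, as an illustration**

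The protocol gives no figure for this point, so there is none to reproduce.

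From the documents: SD 0.25 D (Sample size); 50 children per arm (Randomization); one-sided α = 0.05 (Statistical analysis), critical value 1.645.

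Assumed, with no source in the documents: the fraction *f* of the acupuncture arm removed, 10% or 20%; the amount *k* by which removed children would have done worse than those retained, 0.125 or 0.25 D (0.5 or 1 SD); no children removed from the control arm; a test against zero difference.

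Formulas:

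- Whole-arm mean = retained mean − *f·k*, so removal shifts the acupuncture mean by *f·k*.
- SE = 0.25 × √(1/n₁ + 1/50), with n₁ = 50(1 − *f*). This gives 0.0514 D for n₁ = 45 and 0.0530 D for n₁ = 40.
- Actual one-sided error = 1 − Φ(1.645 − shift/SE).

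| Removed | *k* (D) | Shift (D) | Shift/SE | Error |
|---|---|---|---|---|
| 5 of 50 | 0.125 | 0.0125 | 0.24 | 8% |
| 5 of 50 | 0.25 | 0.025 | 0.49 | 12% |
| 10 of 50 | 0.125 | 0.025 | 0.47 | 12% |
| 10 of 50 | 0.25 | 0.050 | 0.94 | 24% |

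If only 2 of 50 were removed, the shift would be 0.04 × 0.125 = 0.005 D to 0.04 × 0.25 = 0.010 D. With SE 0.0505 D, the error is about 6-7%. With nobody removed it is 5%.

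**4. Dependence on the null**

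Sample size uses a superiority boundary of 0.2. If the final test also uses it, the errors above apply when the true difference equals 0.2 D. With no true difference and a shift of 0.05 D, the estimate would have to exceed its expectation by 1.645 + (0.2 − 0.05)/0.053 ≈ 4.5 standard errors, so the error is negligible.

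**The case against.** The strongest reply is that the rule may reach very few children. The dropout and withdrawal sections retain those who begin and then stop, and guardians of dropouts are to be contacted so that assessments can be completed. Read with those sections, lack of treatment may mean only children never treated. The safety clause in Excluded cases does not settle this, because the children with at least one session may be the mistakenly included ones. This stands, and it limits the likely size. It does not remove the contradiction: a child never treated is still a randomised child, and families who know their allocation can decline to start.

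Three stronger readings are tempting but not supported.

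- A reader might infer that the exclusion can occur *only* in the acupuncture arm. Because the term is undefined and the control text speaks of no *other* treatment, lenses could nominally count as treatment, and a control child without lenses could be caught. *Mainly* is as far as the text goes.
- A reader might take the adherence figure above 80% in Table 2 as a further exclusion. The table lists it as a measure and does not say that anyone is removed for missing it.
- A reader might fault the protocol for not saying which analysis set decides the result. That may be in an analysis plan that is not shown, and reporting both sets is ordinary practice.

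It is also fair to say that the removal fractions, the outcome deficit and its direction are invented for illustration. The 20% in Sample size is a dropout rate, and dropouts are kept, so it cannot be borrowed as the fraction removed.

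**Conclusion.** The contradiction holds. Excluded cases removes randomised children from the efficacy analysis on two grounds, without confining this to the per-protocol set, while Statistical analysis promises intention-to-treat. One ground, "mistakenly included; and lack of treatment" being the pair, is a post-randomisation condition that in practice bears mainly on the acupuncture arm, so the rule as written can bias the primary comparison.

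The size cannot be derived from the protocol. The 8-24% range rests on 10-20% of one arm being removed, on those children doing 0.5-1 SD worse, on no removals among controls, and on a test against zero. With two children removed it is about 6-7%. If the removed children would have done better, the bias would run against acupuncture. The case for correction therefore rests on the conflict in the text and the undefined boundary with dropout, not on a demonstrated large effect.

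**What to change.** Reconcile the two sections:

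1. Define the full analysis set as all randomised children in their assigned arm, whatever treatment they received, and use it for the intention-to-treat analysis of the primary outcome.
2. Confine the lack-of-treatment exclusion to the per-protocol set, as a supportive analysis. Define the term so that it is distinct from dropout.
3. Allow mistaken inclusion to remove a child from the full set only for ineligibility shown by data collected before randomisation, judged blind to arm.

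The cost is wording in two sections. The estimate may be slightly diluted by children who did not attend, and those children have to be kept on the existing visit schedule in Table 1. Trial status reports six participants recruited, so at that stage the change could still be made well ahead of any analysis.

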### Recruitment strategies

The subjects will be informed of the details regarding the trial plan and those who voluntarily participate in the trial will receive free ophthalmologic examinations. Following optometric evaluation, these subjects will receive the highest discount (30% off) on glasses. Subjects in the experimental group will receive a 50% discount on acupuncture treatment. All subjects who receive a follow-up eye exam will not pay a fee and will be permitted to be fast-tracked. The subjects who will be included in the experimental group will receive treatment any time between 10:00 and 19:00 (Beijing time). If adverse events occur during treatment, the treatment will be immediately terminated, and help will be obtained from the emergency department. According to the specific condition which occurs after treatment, a consultation involving at least three experts will be carried out to decide whether or not to continue the clinical trial. Subject compliance will be determined based on whether or not the subject receives due treatment. The researchers will ensure that the subjects in the experimental group fully understand the importance of regular acupuncture and compliance. During the observation period, the use of drugs or other therapies to treat mild-to-moderate myopia will be prohibited.

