**Flow of participants.**

### Recruitment

This study will be conducted in the Department of Ophthalmology, Xinjiang Uygur Autonomous Region Institute of Traditional Chinese Medicine (Xinjiang Medical University Affiliated Hospital of Traditional Chinese Medicine, a grade III level A teaching hospital). Adolescents with mild-to-moderate myopia will be recruited from the 27th Elementary School near the Xinjiang Uygur Autonomous Region Institute of Traditional Chinese Medicine after an ophthalmologic examination. Inclusion criteria will be as follows: the result of retinoscopy is myopic refractive error; distance visual acuity can be corrected to normal using negative spherical or cylindrical lenses; near visual acuity and other visual functions must be normal; myopia diopter spherical lenses must be between -0.5 D and -6.00 D, and cylindrical lenses <1.5 D, as measured under cycloplegia; and adolescents must be between seven and 12 years of age. Exclusion criteria will be as follows: subjects with serious systemic diseases, such as cerebrovascular, liver, kidney, hematopoietic system, and psychiatric diseases; long-term use of other related drugs or treatments, which have not been terminated; diopter < -0.5 D, or combined with pathologic myopia-related fundus changes and/or significant visual function impairment; and the affected eyes have other diseases which affect the determination of acupuncture efficacy.

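### Half the acupuncture fee for 54 daily sessions falls on one unmasked arm, and accepting fee and attendance is not an entry condition, so cost-related refusal can arise after randomisation in that arm alone

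*Protocol article*

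**What the plan says.** All of this is in the protocol article.

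- **Costs (Recruitment strategies).** "Subjects in the experimental group will receive a 50% discount on acupuncture treatment". For participants generally, "these subjects will receive the highest discount (30% off) on glasses", and "All subjects who receive a follow-up eye exam will not pay a fee".
- **Burden (Intervention).** "One cycle of treatment will last for nine days, followed by one day of no treatment", and "Six cycles of treatment will be undertaken continuously for a total of 60 days". For the other arm, "Subjects in the control group will wear SVLs without any other treatment affecting visual acuity".
- **Masking (Study design; Discussion, limitations).** Only the assessor and the statistician are blinded. No sham group is included.
- **Entry (Recruitment).** The inclusion list covers refraction, acuity and other visual function, and closes with "adolescents must be between seven and 12 years of age". The exclusions concern disease, other treatments and ocular findings. Neither list mentions the fee or daily attendance.
- **Leaving.** Withdrawal conditions allows a subject to stop for any reason and takes the last result as final. Standards of dropout cases names among the common causes "lost to follow-up (including the subjects or their guardians who decided to terminate the treatment".
- **Handling.** Dropout cases has the researchers contact guardians, complete the assessments, record the reason and keep the data. Excluded cases takes out of the efficacy analysis those mistakenly included and those lacking treatment. Statistical analysis names intention-to-treat with a per-protocol set and a full analysis set.

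**The concern.** Randomisation makes the arms comparable on the day the envelope is opened. A filter that acts before that moment affects both arms equally and costs only generalisability. A filter that acts afterwards, in one arm, can undo the comparability.

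Here the part-payment and the daily visits both fall after a known allocation, on acupuncture families alone. Families who accept them may differ from those who do not in means, in belief in acupuncture, or in habits such as reading and outdoor time, which the article itself collects at baseline. No corresponding filter acts on controls. What is at stake is the diopter comparison in whoever remains for analysis, most directly in the per-protocol set.

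**Working it through.** **1. Burden by arm (Intervention).** Six cycles of nine treatment days and one rest day: 6 x (9 + 1) = 60 days, which agrees with the stated total. Sessions: 6 x 9 = 54 in the acupuncture arm, 0 in the control arm. The list price is not given, so the sum payable cannot be calculated.

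**2. The plan's dropout allowance (Sample size).** 79 / (1 - 0.20) = 98.75, so 99, which the article rounds to 100. The expected loss is 0.20 x 100 = 20 children, not split by arm. (The article's inputs do not reproduce n = 79 itself; that is a separate matter and nothing here depends on it.)

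**3. Is the issue power or bias?** Assume a true difference 0.1 D beyond the margin (0.3 against 0.2; the 0.3 is an assumption), with the article's SD of 0.25 and one-sided alpha of 0.05:

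- 40 and 40 completers: power 55.7%
- 45 and 35 completers: power 55.2%

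For the same total loss, imbalance hardly changes power. The issue is bias.

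**4. Size of a selection shift.** Let d be the fraction of an arm that leaves and g the difference in mean outcome between leavers and stayers. The arm mean is (1 - d) x stayers + d x leavers, so a completers-only mean differs from it by d x g. The article gives neither quantity, so both are assumed:

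| d (acupuncture) | g = 0.1 D | g = 0.3 D |
|---|---|---|
| 10% | 0.01 D | 0.03 D |
| 40% | 0.04 D | 0.12 D |

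Against the 0.2 D margin this is 0.01/0.2 = 5% to 0.12/0.2 = 60%.

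If controls also lose a fraction d0 with the same g, the net shift is (d - d0) x g. Splitting the 20 expected losses 15 and 5 (30% and 10%, assumed) gives 0.20 x 0.1 = 0.02 D to 0.20 x 0.3 = 0.06 D. An even split gives zero.

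**5. How plausible is the upper end?** g = 0.3 D is 0.3/0.25 = 1.2 of the plan's SDs. With d = 40%, leaving status alone would explain 0.4 x 0.6 x 0.3² / 0.25² = 35% of the outcome variance. That is extreme, so 0.12 D is an outer bound and not an expectation.

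**6. Do the handling rules remove the problem?** Only in part.

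- Following up and analysing children who stop would remove the completers-only shift for those who are actually measured.
- Table 1 schedules no diopter measurement between baseline and month 3. A child who leaves during the 60 days therefore has only a baseline value unless the contact effort succeeds.
- The exclusion for lack of treatment can in practice apply only where there are sessions to miss, which is the acupuncture arm. A family that declines at allocation could be removed from efficacy altogether, despite the intention-to-treat statement.

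**The case against.** The strongest reply is that families are informed before they join. Recruitment strategies says they hear the details of the trial plan and then volunteer. Written consent is taken at baseline, and the Discussion says guardians understand the follow-up requirements through the consent form. That form is not available here, and the article condenses a fuller protocol. A reader might infer that families first learn of the fee once the envelope is open; the article does not show that. What remains is that being informed is not an entry condition: nothing in the criteria makes accepting either allocation, with its fee and visits, a requirement for randomisation.

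The second reply is that dropouts are contacted, their reasons recorded and their data kept, under a named intention-to-treat principle. This is real mitigation and stands, within the limits shown in step 6 of the working.

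Third, a treatment-versus-no-treatment design always puts more burden on one arm, and a single overall dropout allowance is normal practice. Both are fair. A reader might take the undivided 20% as concealing an imbalance, but no imbalance is shown.

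Fourth, the control allocation is not free of cost, since both arms buy glasses at the same discount. That is correct; the asymmetry concerns the sessions only.

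**Conclusion.** The concern holds as a design weakness of unknown size. It rests on five features of the article: half the fee and 54 visits in one arm, an unmasked allocation, freedom to leave for any reason, no entry condition on fee or attendance, and an efficacy exclusion that in practice touches only the acupuncture arm.

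Under the assumptions stated, a completers-only acupuncture mean would shift by 0.01 to 0.12 D against a 0.2 D margin. The upper end needs both heavy selective loss and an implausibly large gap between leavers and stayers. Full follow-up of those who stop would reduce the shift.

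A reader might infer that the bias must favour acupuncture. The article does not support a direction: families worried about fast progression may be the ones who keep paying, which would work against acupuncture. Nor does it support a claim that lens wear is among the recorded characteristics through which selection could be examined. Reading and outdoor time are listed under Data collection and in Table 2; lens wear is not.

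**What to change.** 1. Add an inclusion criterion under Recruitment: before the envelope is opened, the guardian confirms in writing acceptance of either allocation, including the acupuncture fee and the 54 visits.
2. Amend Excluded cases so that all randomised children, including those who do not start or who stop because of cost, stay in the full analysis set.
3. Tabulate by arm the reasons already recorded under Dropout cases, with cost as a category of its own.

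The cost is one criterion, one consent line and one table. Some families will decline before randomisation, so recruitment is slightly slower and the sample slightly more selected, but equally in both arms. Trial status reports six participants recruited, so 94 of the planned 100 could still enter under the new rule.

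The criterion reduces differential dropout but does not remove it, because a signed acceptance does not stop a family leaving later. Waiving the fee would remove the cost asymmetry, though not the attendance burden. It needs funds, and the Discussion describes the budget as limited, so it is an option and not the main recommendation.
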